### Data management

The clinical trial database will be constructed by a designated data manager who will be responsible for regular database management and maintenance. All data will be imported into the clinical trial database by two research assistants. The EDC system automatically generates queries resulting from the computer checks embedded into the system to ensure the accuracy, quality, consistency and completeness of the database. Manual queries resulting from review by monitors, medical coders and other data management staff will also be generated from within the EDC system, where they are tracked. Queries can be resolved, and data entered can be corrected on-site when necessary. Every change to the data will be captured in the EDC system audit trail. Upon the completion of the study or after reaching a prespecified point in the study, data management will lock the database and generate the SAS datasets necessary for data analysis and reporting.

### Confidentiality

The confidentiality measures are as follows: The results of this research project may be published in medical journals. The patient’s information will be represented by a unique number, and the coded information will be stored at the First Hospital of GZUCM. The information of subjects will be maintained confidential as required by law. However, the records of subjects may be reviewed to ensure that the study complies with applicable laws and regulations.

### Plans for collection, laboratory evaluation and storage of biological specimens for genetic or molecular analysis in this trial/future use

Not applicable.

## Statistical methods

### Statistical methods for primary and secondary outcomes

SPSS 22. 0 (IBM, Armonk, NY, USA) software will be utilised for statistical analysis. *P* ≤ 0. 05 will be considered statistically significant.

The primary outcomes will be compared between groups by using Pearson’s chi-squared test. *t*-test, corrected *t*-test (equal variance not assumed), and analysis of variance for repeated measurements will be used for data analysis, and grade data will be assessed via Wilcoxon two-sample test.

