### Intervention description

The patients in the test group will receive one-stage anal fistulotomy surgery combined with SSG, and those in the control group will undergo anal fistulotomy only. All the operations will be performed by attending colorectal surgeons or surgeons at a higher level. During this trial, all subjects will receive general treatment.

The patients in the test group will be on a semiliquid diet and take oral polyethylene glycol electrolyte powder for bowel preparation one night before operation. The patients will be placed in the lateral position after spinal anaesthesia, and their perianal skin will be sterilised. Their tract and internal opening will be probed by using a probe. Then, a strip of skin with a size of 1. 0 cm × 3.0 cm will be incised and freed below the dental line along the fistula and distal to the outer side of the anus without cutting its end (Figs. 2 and 3). The probed tract will be opened and scraped (Figs. 4 and 5), and the inflamed tissue will be removed. Some tissue will be retained for biopsy. Wound bleeding will be stopped by electrocoagulation if necessary, making the harvested skin from the surgical region into full-thickness skin (Fig. 6) and grafting it at the wound closely without tension by stitching with 4–0 Coated Vicryl (Figs. 7 and 8). The wound will be covered with petrolatum gauze and sterilised dressing. All the patients will be given celecoxib one piece at a time twice a day to relieve pain for 7 days. Patients will be advised to go on semiliquid diets and control bowel movements for 3 days. The wound will be cleaned gently with warm water after every bowel movement. Patients will be followed-up on the 3rd day, 7th day, 14th day, 21–22nd day, 27–29th day, 2nd month, 3rd month and 6th month postoperation in clinic visits.

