### Outcomes

#### Primary outcomes

Wound healing time, wound exudation rate, cure rate during 14 days postoperation, recurrence rate during 3 months and total cure rate. The wound is regarded as cured when the grafted skin survives, and the wound has epithelised completely. Wound exudation will be rated on the basis of the number of times dirty underwear or sanitary pads are changed during 1 day.

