### Sample size

This study is a superiority trial. Our pretest showed that the average wound healing times of the graft and no-graft groups were approximately 15 and 25 days, respectively. We assume that no difference in efficacy exists among the three centres. Assuming a two-sided significance level of 0. 05 and power of 80% (*α* = 0. 05, *β* = 0. 2), the sample size is calculated as 47 (fixed model as $$n_{1} = n_{2} = \frac{{\sigma^{2} \left( {{\text{t}}_{\alpha } + t_{\beta } } \right)^{2} }}{{\delta^{2} }}$$) [11]. Considering a loss to follow-up of 10%, the sample size for each group is 52 cases, and the total is 104 cases.

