### Plans to promote participant retention and complete follow-up

Follow-up will be conducted at baseline, at 1 week ± 3 days, 2 weeks ± 3 days, 3 weeks ± 3 days, 4 weeks ± 3 days, 8 weeks ± 3 days and 12 weeks ± 3 days and 24 weeks ± 3 days. Any missing or incorrect data will be detected by the software system. In such a case, the original CRFS will be checked to correct or complete every piece of data.

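### Wound healing time, the outcome that sizes the trial, is assigned a test for proportions that cannot test or estimate the planned difference in days

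*Protocol article*

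**What the plan says.** Under Primary outcomes the article lists five: "Wound healing time, wound exudation rate, cure rate during 14 days postoperation, recurrence rate during 3 months and total cure rate". The first is a time in days and the other four are called rates.

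Under Sample size, only healing time is used: "Our pretest showed that the average wound healing times of the graft and no-graft groups were approximately 15 and 25 days, respectively". A formula for means gives the group size ("the sample size is calculated as 47"), which is then raised for loss: "Considering a loss to follow-up of 10%, the sample size for each group is 52 cases, and the total is 104 cases".

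Under Statistical methods for primary and secondary outcomes, the assignment is "The primary outcomes will be compared between groups by using Pearson’s chi-squared test", with no exception. The next sentence names the t-test, its unequal-variance form and repeated-measures analysis of variance without attaching any of them to an outcome. It gives the Wilcoxon test to graded data. No time-to-event method appears there or under the additional analyses.

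Visits are described three times. Intervention description has days 3, 7 and 14, short ranges around days 21 and 28, then "2nd month, 3rd month and 6th month postoperation in clinic visits". Recruitment gives the same visits as single days. The retention section starts at week 1, has no day-3 visit, and puts the same tolerance on every visit: "2 weeks ± 3 days, 3 weeks ± 3 days, 4 weeks ± 3 days, 8 weeks ± 3 days", and likewise at weeks 12 and 24.

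**The concern.** The design and the analysis do not meet. The sample size is for a difference in mean days, while the assigned test needs categories, and none are defined for healing time. Taken literally, the analysis returns a p-value for a cut-point chosen later and no estimate in days, although shortening healing time is the reason for the trial.

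The obvious repair, a t-test on days, needs one exact healing day for every patient. The article defines when a wound counts as healed but not how the day is dated. It also does not say what value a patient still unhealed at last contact receives. Review is weekly up to day 28 and about monthly or sparser afterwards, and with assumed means of 15 and 25 days the sparse part falls mostly on the control arm. Such choices move the estimate in days and can be made after the data are seen.

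**Working it through.** **1. The plan's own figure.** Inputs from Sample size: difference 25 − 15 = 10 days, two-sided alpha 0.05, power 80%, n = 47 per group. No SD is stated, so 47 can only be solved backwards. With z = 1.960 + 0.842 = 2.802 and z² = 7.849:
- printed formula, n = σ²z²/δ²: σ = 10 × √47 / 2.802 = 24.5 days;
- standard two-sample formula, n = 2σ²z²/δ²: σ = 10 × √(47/2) / 2.802 = 17.3 days.

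Loss: 47 × 1.1 = 51.7, so 52 per group and 104 in total. On either formula the quantity planned for is a difference in means.

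**2. What chi-squared would do.** It needs a cut. With gamma times (assumed), means 15 and 25, SD 17.3 and 47 per group:
- healed by day 14: 63.0% against 30.1%, power 91%;
- healed by day 28: 83.5% against 65.5%, power 52%.

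Power therefore depends on a cut-point the article does not define, and neither version estimates the 10 days.

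**3. What a t-test on days would do.** Assumptions: log-normal times with means m = 15 and 25 and a common SD from 5 to 17. Parameters: s² = ln(1 + (SD/m)²), μ = ln m − s²/2.

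Share healing after day 28 = 1 − Φ((ln 28 − μ)/s):
- SD 5: graft μ 2.655, s 0.325, 1.9%; control μ 3.199, s 0.198, 25.1%;
- SD 17: graft μ 2.295, s 0.909, 12.7%; control μ 3.029, s 0.617, 31.1%.

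Simulated differences in days (true value 10). Grid A is days 3, 7, 14, 21, 28, 60, 90, 180. Grid B is days 7, 14, 21, 28, 56, 84, 168, from the retention section without its windows.

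| SD | First healed visit, grid A | First healed visit, grid B | Exact times, unhealed at day 28 left out |
|---|---|---|---|
| 5 | 15.6 | 14.6 | 8.1 |
| 8 | 15.1 | 14.1 | 7.3 |
| 10 | 14.5 | 13.7 | 7.0 |
| 12 | 14.2 | 13.3 | 6.8 |
| 17 | 13.7 | 12.9 | 6.2 |

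On grid A at SD 5 the recorded means are 18.9 and 34.5 days, so the control mean is pushed up by 9.5 days and the graft mean by 3.9. With gamma times the left-out version gives 9.1 days at SD 3. Dating at the interval midpoint (gamma, grid A, SD 3 to 24.5) gives 10.5 to 12.8 days.

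**4. Visit windows.** Week 2 with a tolerance of 3 days runs from day 11 to day 17. With normal times in the graft arm (mean 15), the share healed at those two days is Φ((11 − 15)/SD) and Φ((17 − 15)/SD): 21% and 66% at SD 5, 34% and 58% at SD 10. These are the edges of the window, not typical visits.

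**The case against.** A fair reader could take chi-squared to be meant for the four rates and a t-test for healing time. That may be the intention, but the text assigns chi-squared to the primary outcomes without exception and links the t-tests to nothing.

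A reader might infer that the trial will overstate its benefit. The document does not support that. It never says healing is dated at the visit; this is only inferred from the schedule and from wound photographs being tied to follow-up. Chi-squared gives no difference in days to overstate. Leaving out unhealed patients moves the estimate the other way. The 15 and 25 days from the pretest may themselves have been read at visits, in which case rounding them up again counts the effect twice. If both arms are read on the same grid, the comparison also stays valid when there is no effect; only the size of the estimate suffers.

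A reader might also infer that unhealed patients are mishandled. The article provides an analysis set of all randomised patients and multiple imputation for missing values. What is absent is a rule for someone known to be unhealed at last contact, and a full protocol or analysis plan may hold it. In the models above, non-healing by 6 months is at most about 0.4% per arm, so most censoring would come from the 10% loss allowed for.

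The visit-schedule conflict is a separate and smaller matter. A window of 3 days is not an error in itself, and nothing suggests that it would be used differently by arm.

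**Conclusion.** The mismatch stands on the text alone: the outcome that sizes the trial is given a test that cannot address the planned difference, and no listed alternative is assigned to it. It should be corrected before the analysis.

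The figures in days are conditional. Visit dating would turn 10 days into about 13 to 16, and omitting patients unhealed at day 28 would turn it into about 6 to 8 (up to 9 at smaller spreads). Both rest on assumed distributions and SDs. They do not predict a bias in one direction. They show why naming a t-test would not settle the matter and why a method that uses intervals and censoring is preferable.

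The conflict between the visit schedules is real but secondary. It matters mainly because 14-day cure is itself a primary outcome.

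**What to change.** - Restrict Pearson's chi-squared, with Fisher's exact test where expected counts are small, to the binary outcomes, including 14-day cure.
- Assign wound healing time a time-to-event comparison in all randomised patients. Preferably treat it as interval-censored between the last visit not healed and the first visit healed, using actual visit dates, and right-censor patients not healed at last contact. Report the difference in median or restricted mean time with a 95% confidence interval.
- Reconcile Intervention description, Recruitment and the retention section on the day-3 visit and the window widths.
- Recheck power. As a log-rank illustration with Weibull times, the hazard ratio is (25/15)^shape and the events needed are 4 × 7.849 / (ln HR)²: 121 at shape 1 (more than the 104 patients; 70% power with 94 events), 78 at shape 1.25, 54 at shape 1.5 and 31 at shape 2. Whether 104 patients suffice depends on the spread, so the pretest SD should be stated.

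The cost is wording, some programming and a revised power statement. The article names SPSS 22.0 for analysis and SAS datasets at database lock, so the software for this analysis should be named. No extra visits are needed, provided actual visit dates and healed status at each visit are recorded. The change should be dated before unblinding; if unblinding has already happened, it must be reported as made afterwards.

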### Interim analyses

Colorectal surgeons will have access to interim results and make the final decision to terminate the trial.

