## Assignment of interventions: blinding

### Who will be blinded?

A total of 104 eligible subjects will be randomly assigned to two parallel groups. Statisticians will adopt the SAS randomisation programme to generate a randomisation list. Then, the clinical trial manager will divide the patients into two groups in accordance with the randomisation list. All people involved, including the investigators, will be blinded to the assignment of the subjects. The relevant procedures and allocations will be given to the patients by the surgeons in accordance with the randomly generated numbers at different stages. All the study field personnel, patient, sponsor and contract research organisation will remain blinded in the study.

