### Methods for additional analyses

The hybrid control will use multivariate logistic regression and odds ratio and 95% confidence interval estimation. Clinically significant variables from the univariate analysis will be included in the multivariate model. Goodness-of-fit will be evaluated through the Hosmer–Lemeshow test. Statistical analysis will be performed by using SPSS 22.0. A two-tailed significance level of 0.05 will be used for all tests. *P* < 0.05 will indicate statistical significance.

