### Composition, role and reporting structure of the data monitoring committee

The data monitoring committee will include three members, namely an EDC system administrator, a data administrator and a statistician. The committee is independent of the research team and has no conflict of interest with the investigators. They will perform data management design, processing and regulation, quality control, security and confidentiality measures and EDC system management.

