#### Dissemination plans

All presentations will protect the integrity of the primary research objectives. None of the data that compromise blinding will be released before results are available. The steering committee will discuss the recommendations on the timing of these final data that may be presented at the meetings. The primary outcomes will be published in abstract books and articles.

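### The interim rule gives unspecified colorectal surgeons the results and the final stopping decision, without limiting the reason for stopping or naming an independent reviewer

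*Protocol article*

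**What the plan says.** The section on interim analyses in the protocol article reads in full: "Colorectal surgeons will have access to interim results and make the final decision to terminate the trial". It sets no purpose for the look and no limit on the grounds for stopping, and it does not identify the surgeons.

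Other sections bear on it:

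- **Who will be blinded?** "All people involved, including the investigators, will be blinded to the assignment of the subjects". The same section keeps field staff, patients, sponsor and contract research organisation blinded.
- **Roles of colorectal surgeons.** They perform the operations (Intervention description), obtain written consent (Who will collect informed consent?) and record baseline data (Recruitment).
- **Data monitoring committee.** It consists of an EDC administrator, a data administrator and a statistician. It is described as independent ("The committee is independent of the research team and has no conflict of interest with the investigators"), but its listed duties are data management, quality control, security and EDC administration.
- **Steering committee.** It consists of two senior colorectal surgeons and a statistician, also described as independent of the research team, who supervise the trial. No interim review or stopping role is stated.
- **Significance level.** Two-sided 0.05 in Sample size, P ≤ 0.05 for the primary and secondary outcomes, and under Methods for additional analyses: "A two-tailed significance level of 0.05 will be used for all tests".

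**The concern.** This is a rule the protocol states, not a detail it leaves open. It allocates interim access and stopping authority to a group defined only by specialty, and in this trial that specialty covers the people who recruit and treat.

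A surgeon who knows the emerging between-arm difference may, without intending to, change whom he or she approaches for consent. Investigators may also remove patients they judge ineligible or unsuitable to continue (Withdrawal criteria; Criteria for discontinuing or modifying the allocated interventions), so the same knowledge can affect who stays in the trial. No body separate from recruitment and treatment is assigned to review the comparison.

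The second issue is the false-positive rate. The rule leaves open stopping because the graft arm looks better. If such a look used the ordinary 0.05 threshold, the final 0.05 would no longer be the true error rate, and a trial stopped on an early high would tend to overstate the effect.

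**Working it through.** **1. Who holds access, compared with who must be blinded.** There are two readings of the interim sentence.

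- *Trial surgeons.* They operate, consent and record baseline data. By-arm interim results would break the statement that all people involved are blinded.
- *The two steering-committee surgeons.* They are independent of the research team, so the recruitment risk largely disappears. The interim sentence does not name the committee, however, and the literal wording on blinding would still need an exception for them.

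If the interim results were pooled over arms, neither reading would breach blinding. The text does not say whether they are pooled.

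**2. The plan's own sample-size figure.** Inputs from Sample size: "average wound healing times of the graft and no-graft groups were approximately 15 and 25 days, respectively", so the difference is 10 days; two-sided α = 0.05; power 80%; 47 per group, 52 after 10% loss, 104 in total. The standard deviation is not given, so 47 cannot be independently reproduced. The standard two-sample formula n = 2σ²(z₀.₉₇₅ + z₀.₈₀)²/δ² returns 47 if σ = 10 × √(47/2)/(1.960 + 0.842) ≈ 17.3 days. For the loss, 47 × 1.1 = 51.7, which rounds up to 52. The calculation is for a single final test at 0.05.

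**3. Type I error if looks can stop for efficacy at 0.05.** The number, timing and purpose of looks are not stated, so these are assumed scenarios. Under the null hypothesis the test statistics at information fractions tᵢ < tⱼ have correlation √(tᵢ/tⱼ). The overall error is 1 − P(|Zₖ| ≤ 1.96 at every look), with the final test included, by multivariate-normal integration:

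| Interim looks | Timing | Overall two-sided error |
|---|---|---|
| 0 | final only | 0.050 |
| 1 | 25% | 0.091 |
| 1 | 50% | 0.083 |
| 1 | 75% | 0.073 |
| 2 | equally spaced | 0.107 |
| 4 | equally spaced | 0.142 |

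Simulation of the equally spaced cases agrees (0.083, 0.107, 0.142).

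**4. If looks can stop only for safety or futility.** Success can then be declared only at the final test, so the overall error stays at or below 0.05.

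**5. A boundary that holds 0.05 with one half-way look.** O'Brien-Fleming-type spending at t = 0.5 uses 4 × [1 − Φ(2.241/√0.5)] = 0.0031 at the look (|Z| > 2.963). Solving for the final critical value at overall 0.05 gives |Z| > 1.969, that is p < 0.049. The classical O'Brien-Fleming pair is 0.0052 and 0.048. Keeping 80% power under the spending version multiplies the sample size by 1.004: 47 × 1.004 = 47.2, at most 48 per group.

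**The case against.** The strongest reply is that the sentence says little, and that most of the alarm comes from what a reader adds to it. Five parts of that reply carry weight.

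- **Efficacy stopping is not stated.** A reader might infer that the plan inflates type I error. The documents do not support that: no efficacy test, threshold or schedule is given for the look, and termination could be for safety or futility only.
- **A boundary may exist elsewhere.** The article condenses a fuller protocol, and an analysis plan may exist. The absence of a boundary is therefore no finding in itself. A general 0.05 is also how an overall level is normally written, and the statement about all tests sits under additional analyses.
- **Sole control is not stated.** A reader might infer that surgeons decide alone. The text gives them the final decision and names no other body, but does not say that nobody advises them. They may be the steering-committee surgeons.
- **The dissemination statement is not a contradiction.** "None of the data that compromise blinding will be released before results are available" appears under Dissemination plans and concerns presentation and publication, not internal review.
- **Biased wound assessment is not the main risk.** Evaluations are assigned to an assistant involved in neither randomisation nor treatment. Operating surgeons also necessarily know which procedure they performed, so part of the blinding problem lies in the blinding statement itself.

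These points narrow the concern but do not remove it. Knowing one's own cases is different from seeing the comparison across three centres and holding the decision to stop. The sentence still assigns both to an undefined group that includes recruiters, with no limit on purpose.

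**Conclusion.** The concern holds in a limited form. The interim rule is badly fixed: it does not say which surgeons, what they see or why they may stop, and it is connected to neither committee. If trial surgeons receive by-arm results, it conflicts with the blinding statement and opens a route to bias through recruitment and withdrawal.

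The type I error figures are illustrations. They require that a look can stop the trial for efficacy, that each look and the final test use two-sided 0.05, and the number and timing of looks shown. On those terms the overall error is about 8.3% with one half-way look and 10.7% with two. With safety-only or futility-only stopping there is no inflation. The documents do not settle which case applies.

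**What to change.** Reword the interim section as follows:

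1. Only the independent steering committee, with its statistician, sees comparative interim results and recommends stopping. Operating and recruiting surgeons do not. Amend the blinding statement to allow this exception.
2. Either state that there is no stopping for efficacy and that the final test is at two-sided 0.05, or allow one look at half the information with an O'Brien-Fleming-type boundary (about 0.003 at the look, 0.049 at the end). State that a safety-only review spends no alpha.

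The cost is wording and assigning a role to a committee that already exists. If the look is kept, the final threshold drops from 0.05 to 0.049 and the sample size needed rises by about 0.4%.

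The Trial status section expected completion by 24 October 2022, and the article appeared on 22 July 2023, so a prospective change may no longer be possible. In that case, report whether any interim look took place, who saw it, whether it was split by arm and for what purpose. If stopping for efficacy was possible, adjust the final inference for it.
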